### Objectives {7}

The overall objective of this trial is to evaluate the impact and acceptability of digital CBTI hubs to augment military treatment facilities’ capabilities in behavioral sleep medicine and maintain high-quality clinical outcomes. The specific aims are to (1) examine and compare the changes in insomnia severity at baseline, at 6–8 weeks, and at 3-month follow-up; (2) examine and compare the changes in daytime symptoms of depression and anxiety at baseline, at 6–8 weeks, and at 3-month follow-up; and (3) examine and compare patient satisfaction with ICAU versus CBTI via a digital CBTI hub.

The first hypothesis is that improvements in insomnia symptom severity in service members with a diagnosis of chronic insomnia following remote, asynchronous delivery of CBTI via a digital CBTI hub will be non-inferior to improvements detected following ICAU after 6–8 weeks and at 3-month follow-up. The second hypothesis is that improvements in daytime symptoms of depression and anxiety in service members with a diagnosis of chronic insomnia following remote, asynchronous delivery of CBTI via a digital CBTI hub will be non-inferior to improvements detected following ICAU after 6–8 weeks and at 3-month follow-up. The third hypothesis is that satisfaction with insomnia care following treatment through a digital CBTI hub will be non-inferior to ICAU.

### Trial design {8}

This is a multi-site phase II, parallel, non-inferiority randomized clinical trial that aims to compare the short- and medium-term effects of ICAU at three military sleep clinics versus CBTI delivered remotely through digital CBTI hubs. ICAU and the digital CBTI hubs will be evaluated and compared on an insomnia outcome measure as well as patient-rated treatment satisfaction and daytime mood and anxiety symptoms. In alignment with the pragmatic nature of this study and, if successful, the aim to rapidly inform insomnia care practices, this trial is designed to minimize disruption of each sites’ current processes for the diagnosis of insomnia and subsequent insomnia treatment procedures. All sites will follow their standard procedures for service members with complaints of sleep disturbances to obtain an appointment with the site’s sleep medicine clinic for an initial evaluation. Following this appointment, service members who receive a diagnosis of chronic insomnia by their sleep medicine provider and who would otherwise be referred (internally or externally) for CBTI will be referred to the study. After providing informed consent, eligible participants will complete baseline assessments including validated self-report questionnaires on insomnia, anxiety, depression, and sleepiness. Participants will then be randomized to either ICAU or insomnia care delivered via a digital CBTI hub. ICAU will be delivered synchronously, in-person (face-to-face or virtual) according to each site’s current standard of care and in the real-world clinical practice setting by a non-research clinician. While there are practice overlaps across sites, some variation exists in procedural and clinical treatment approaches and delivery formats (e.g., required attendance at a sleep seminar in addition to individual sessions, emphasis given to the cognitive component of CBTI, in-person versus synchronous telehealth, and scheduled session frequency). To maximize the generalizability of findings to current clinical practices, ICAU will not be standardized across sites or clinicians. All ICAU clinicians will deliver insomnia care to study participants as they would otherwise treat patients with chronic insomnia who are not participants in this clinical trial. Insomnia care delivered via the digital CBTI hubs includes the first-line recommended treatment for insomnia, CBTI, delivered remotely and asynchronously with NOCTEM’s clinical decision support platform called COAST by a NOCTEM-certified and licensed clinician. A follow-up will be conducted with participants randomized to both treatment arms 6–8 weeks after baseline and again 3 months later.

## Methods: participants, interventions, and outcomes

### Study setting {9}

The study will be conducted with service members across three military treatment facilities in the USA. The three military treatment facilities have a dedicated sleep clinic with at least one behavioral sleep medicine provider (physician and/or psychologist) and existing procedures and personnel for insomnia treatment.

### Eligibility criteria {10}

Potential participants will be identified by their sleep medicine provider during regularly scheduled appointments with the sleep clinic at their military treatment facility. The sleep medicine provider will only inform patients about the study who are active duty service members, at least 18 years old, have a current diagnosis of chronic insomnia, and are deemed appropriate for a course of CBTI. As service members often present with psychiatric and medical conditions that are commonly comorbid with chronic insomnia (e.g., depression, hypertension, obstructive sleep apnea), they will be eligible if these conditions are adequately treated or managed, including using medication(s) that has been unchanged for at least 1 month and will remain unchanged for the acute intervention phase. Service members using prescribed sleep medications will also be eligible to participate in the trial if they have been on the same medication(s) and at the same dose(s) for at least 1 month, and there are no expected changes over the course of the acute intervention phase. Medication usage and changes will be tracked prospectively and be considered in the analytical plan should changes occur.

Service members will be excluded from participation if they present with an untreated or under-treated comorbid sleep disorder that requires independent treatment or that may be exacerbated by CBTI interventions (e.g., obstructive sleep apnea, rapid eye movement (REM) sleep behavior disorder, or sleepwalking with a history of injury to self or others). Individuals will also be excluded if they are determined to be in acute psychiatric distress associated with marked impairments in functioning or that limits engagement in CBTI, adversely impacts the risk/benefit ratio of participating in the study, or requires immediate attention (e.g., attempted suicide in the past 6 months, seeking and/or receiving psychiatric treatment that requires inpatient or partial hospitalization level of care, requiring support of an assigned case manager for activities of daily living, active substance use disorder, past or current diagnosis or sub-threshold symptoms of psychotic or bipolar disorders, and untreated seizure disorder). Breastfeeding women or parents of an infant under the age of 3 months will also not be eligible, as their insomnia is confounded by these conditions, and CBTI may create greater-than-expected levels of transient sleepiness or fatigue. These minimal exclusion criteria are designed to support the recruitment of participants who are representative of adults with chronic insomnia and generalizable to real-life findings for military and civilian populations. The exclusion criteria that have been established are intended to minimize the risks associated with study participation. Nonetheless, each referring sleep medicine provider will use their clinical judgment to make determinations about the appropriateness of study participation, including CBTI for the patient, and will determine whether a patient is eligible for the study.

### Who will take informed consent? {26a}

After being informed of the study by their sleep medicine provider, service members who express interest in participating in the study will be informed of how to contact the site research coordinator directly or may agree to be contacted by the site research coordinator. At their first contact with the coordinator, the coordinator will review details about the study aims, procedures, and risks following a script to verify the consistency and completeness of the information provided. They will also answer any questions the potential participant may have about the study. If the person declines participation, the coordinator will contact the referring sleep medicine provider to let them know that the patient should be scheduled for follow-up care at the local sleep clinic. For participants who remain interested in participating in the study, after receiving information about the study and obtaining answers to questions that may have arisen, oral consent will be obtained to conduct a brief screening interview to confirm eligibility. Upon verification of eligibility, participants who express the desire to participate in the study will then review the consent form with the coordinator.

### Additional consent provisions for collection and use of participant data and biological specimens {26b}

As part of the informed consent, participants will confirm agreement to have their de-identified data maintained for future use, which may include further analysis and comparison of the dataset created in this study to others.

### Interventions

#### Explanation for the choice of comparators {6b}

As a non-inferiority trial, this study is designed to assess if digital CBTI hubs are no worse than the current standard therapy being offered to patients with chronic insomnia in military treatment facilities [39]. As such, we selected to compare the digital CBTI hubs to the current insomnia treatment practices (insomnia care as usual (ICAU)) at participating military treatment facilities.

#### Intervention description {11a}

Both intervention delivery formats, ICAU, and digital CBTI hubs using COAST will be delivered by credentialed masters or doctoral-level clinicians with experience in behavioral sleep medicine and include CBTI techniques. CBTI is a multi-component manualized cognitive-behavioral treatment protocol for the treatment of insomnia that is widely available. Among the various techniques that can be combined into CBTI, the most effective techniques to reduce insomnia are stimulus control and sleep restriction [40, 41]. Stimulus control aims to limit the use of the sleep environment (bed, bedroom) to sleep and directly addresses behaviors that disrupt circadian sleep–wake regulation mechanisms [42–44]. Sleep restriction involves the implementation of a regular sleep–wake schedule, which limits the time spent in bed while awake [45]. Relaxation techniques (e.g., progressive muscle relaxation, deep breathing, guided imagery) may also be helpful to reduce cognitive or physical hyperarousal that delays sleep onset [17].

Specifically, ICAU will include the usual care for service members diagnosed with insomnia at their local military treatment facility, as per the site’s current clinical practices. Treatment sessions will be conducted with the treating clinician(s) who typically receive insomnia referrals. Across sites, treatment duration will range from approximately 6 to 12 weeks with appointments scheduled every 1 to 3 weeks. Sleep metrics and progress will be evaluated and assessed by sleep diary, validated measures such as the Insomnia Severity Index and Epworth Sleepiness Scale, and patient self-report during scheduled sessions. All sessions will be conducted synchronously and in person (face-to-face, virtually). Patients may be required to attend a single sleep hygiene group seminar where foundational healthy sleep habits and relaxation skills are reviewed.

Treatment via a digital CBTI hub includes CBTI delivered remotely and asynchronously via NOCTEM’s proprietary software platform COAST (Clinician Operated Assistive Sleep Technology) with a NOCTEM research clinician. All research clinicians are fully credentialed, licensed healthcare professionals certified in the use of COAST by NOCTEM. COAST is an adaptive digital health system that includes a clinician portal for prospective monitoring of side effects, progress, and adherence and algorithm-generated recommendations for the implementation of CBTI techniques; a patient application (“app”) with embedded sleep educational materials and self-report daily sleep diary and weekly assessments; and a secure HIPAA-compliant two-way messaging system that allows patients and clinicians to communicate directly in case of questions. Treatment sessions will be conducted across 6–8 weeks, with asynchronous clinical interactions occurring throughout the 6–8-week period with at least one interaction per week. Minimally, each week, the research clinician will send personalized recommendations for behavioral changes to the participant via the app and instruct the participant to review specific sleep tactics (written or audio CBTI interventional materials) that provide instruction on how to implement and the background for the CBTI techniques. Dialog regarding these recommendations will primarily be conducted via the COAST messaging system; however, at any time during the intervention, the participant or the clinician may request a synchronous telephone or in-person appointment.

#### Criteria for discontinuing or modifying allocated interventions {11b}

All clinicians will use their clinical judgment to assess the ongoing appropriateness of the participant for CBTI. Should it be determined that the participant is no longer a good candidate for CBTI, the participant’s treatment will be discontinued, and study participation terminated.

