#### Relevant concomitant care permitted or prohibited during the trial {11d}

Participants may receive care for comorbid psychiatric and medical conditions to the extent that eligibility criteria for the trial continue to be met. Specific details are provided above in the “Eligibility criteria {10}” section.

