### Assignment of interventions: blinding

#### Who will be blinded {17a}

Given the nature of the study design, blinding of participants or clinicians will not be possible. However, masked data will be provided to the biostatistician who will perform the analyses. Randomization will be unmasked only after analyses are finalized. Furthermore, clinicians providing ICAU or treatment via digital CBTI hubs will not participate in periodic interim analyses of the primary and secondary outcomes to avoid biases and/or changes in practice over the course of the study.

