Our primary strategy will compare digital CBTI hubs and ICAU using analyses that are straightforward and highly interpretable while still accounting for other important covariates. We will use analysis of covariance (ANCOVA) to determine whether ISI at 6–8 weeks and at 3-month follow-up differs between digital CBTI hubs and ICAU after controlling for baseline ISI and other relevant covariates. Cohen’s *d* effect sizes (*d* ESs) with 95% CIs estimated from the ANCOVA model will be calculated and compared to the NIM as outlined above. To examine more nuanced effects across time, we will calculate the rate of change in ISI symptoms (ΔISI) across baseline, 6–8 weeks, and 3-month follow-up for each individual and then use linear regression to compare ΔISI between digital CBTI hubs and ICAU after controlling for relevant covariates. We will also model the repeatedly measured outcome using mixed effects models with a random intercept and slope. Cohen’s *d* ESs and 95% CIs estimated from these models will be calculated and compared to the NIM as outlined above.

For non-inferiority tests, we set an allowable one-sided type I error rate of *α* = 0.025. Conservatively adjusting for our two a priori *t*-tests (6–8 weeks and 3-month follow-up), we use *α** = 0.0125 to determine power. Our full sample size of 94 per group will provide 0.88 power. However, even with attrition of 25% (*N* = 70 completers per group), we expect to have 0.80 power. We will use the same statistical approach to assess and compare changes in depression and anxiety symptom severity at 6–8 weeks and at 3-month follow-up.

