### Methods in analysis to handle protocol non-adherence and any statistical methods to handle missing data {20c}

The primary analytic approach will be based on intent-to-treat principles and will include all individuals regardless of adherence to protocol, although “per-protocol” sensitivity analyses will also be conducted to evaluate the robustness of our findings. Missing observations will be investigated to determine the underlying mechanism (missing at random, completely at random, not at random) so that appropriate methods for handling the missing data can be employed.

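### Ending study participation together with treatment loses outcomes that the intent-to-treat analysis promises to include; the size and direction of any bias are unknown

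*Protocol article*

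**What the plan says.** Section {11b} of the protocol article leaves the decision to the treating clinician: "All clinicians will use their clinical judgment to assess the ongoing appropriateness of the participant for CBTI". If the answer is no, "treatment will be discontinued, and study participation terminated". The section gives no criteria and does not mention later assessments. Provisions for post-trial care {30} deals only with the further clinical care of such participants.

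Section {20c} states that the primary analysis follows intent-to-treat principles and "will include all individuals regardless of adherence to protocol". On missing data it says: "Missing observations will be investigated to determine the underlying mechanism (missing at random, completely at random, not at random"), after which a suitable method is to be chosen.

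The primary analysis in {20a} is an ANCOVA of whether ISI "at 6–8 weeks and at 3-month follow-up differs between digital CBTI hubs and ICAU after controlling for baseline ISI". The same section also plans mixed effects models with a random intercept and slope. The follow-up schedule in {8} is general: "A follow-up will be conducted with participants randomized to both treatment arms 6–8 weeks after baseline and again 3 months later". Section {17a} states that "blinding of participants or clinicians will not be possible".

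**The concern.** An intent-to-treat analysis needs outcomes from everyone randomised, including those who stop treatment. Section {11b} makes stopping treatment and leaving the study the same event. This is a rule of conduct, so an analysis plan that is not shown cannot undo it: outcomes that were never collected cannot be analysed.

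Removal could also differ between arms. ICAU is given by non-research clinic staff at appointments every 1 to 3 weeks. The hub is run by research clinicians of the platform's developer, with at least one interaction a week and prospective monitoring through the portal. All of them know the allocation, and each uses their own judgment.

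In a non-inferiority trial, losing more poorly performing participants from the hub than from ICAU would make the hub look closer to ICAU than it is, which favours the claim under test.

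**Working it through.** **1. The passages side by side.** A participant stopped before 6–8 weeks has a baseline ISI and no later one. A participant stopped between the two assessments has the 6–8 week value and lacks the 3-month value. Section {20c} counts both in the primary analysis, while {11b} ends their participation. The general schedule in {8} names both arms but does not address participants already terminated.

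**2. The plan's own figure.** Inputs from {14}: margin d = 0.5, one-sided α = 0.0125, 94 or 70 per group. A true difference of 0 is an assumption, since none is stated.

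Power = Φ(0.5 × √(n/2) − 2.241)

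- n = 94: 0.5 × √47 = 3.428; 3.428 − 2.241 = 1.186; power 0.882. The stated 88% is reproduced.
- n = 70: 0.5 × √35 = 2.958; 2.958 − 2.241 = 0.717; power 0.763 (0.755 with the t distribution). The stated 80% is not reproduced; it would need 77 to 78 per group.

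The second line is a separate matter. It bears on this point only in that lost outcomes cost more power than the article says.

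**3. Shift in a complete-case contrast.** Let pH and pI be the shares terminated in hub and ICAU, and g the number of SDs by which terminated participants are worse than those who stay in the same arm. Each arm's full mean is the stayers' mean plus p × g, so

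true difference = observed difference + g × (pH − pI).

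All three inputs are assumptions, because the article gives none of them. The difference is hub minus ICAU, with positive values worse for the hub and non-inferiority declared when the upper limit is below 0.50, as in the worked example in {20a}.

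**4. False claims of non-inferiority.** For a true d of 0.5, the chance of a false claim is Φ(shift/SE − z), with SE = √(1/n1 + 1/n2), n1 = 94(1 − pH) and n2 = 94(1 − pI). For 10% versus 5% with g = 1: n1 = 84.6, n2 = 89.3, SE = 0.152, and Φ(0.05/0.152 − 1.96) = 0.052.

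| Hub / ICAU terminated | g | Shift towards non-inferiority (SD) | False claim, nominal 0.025 | False claim, nominal 0.0125 |
|---|---|---|---|---|
| 5% / 5% | 1 | 0 | 0.025 | 0.0125 |
| 10% / 5% | 0.5 | 0.025 | 0.036 | 0.019 |
| 10% / 5% | 1 | 0.05 | 0.052 | 0.028 |
| 15% / 5% | 0.5 | 0.05 | 0.051 | 0.028 |
| 15% / 5% | 1 | 0.10 | 0.095 | 0.056 |
| 5% / 15% | 1 | −0.10 | not calculated | not calculated |

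Equal rates with equal gaps give no shift. When ICAU loses more, the bias runs against the hub.

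**5. Determining the mechanism.** Whether data are missing at random or not at random depends on the values that were not seen. Two models that fit the observed data equally well can differ on exactly that. Diagnostics can count against missing completely at random, but they cannot settle the other distinction.

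**The case against.** Several stronger readings are tempting, and the documents do not support them.

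- **That those removed are treatment failures.** Section {11b} is triggered by unsuitability for CBTI. It does not mention non-response, missed sessions or poor adherence. A poor ISI outcome in this group is plausible, but no reasons or outcomes are given.
- **That all their post-baseline data are lost and the ANCOVA drops them.** ICAU runs for about 6 to 12 weeks, so a termination can follow the 6–8 week assessment, and nothing says that data already collected are discarded. Complete-case analysis is not specified either, and an intent-to-treat set can contain people with missing outcomes.
- **That the bias favours the hub and reverses the result.** The planned 25% attrition is all-cause and applied equally to both arms. With 70 per group and an observed d of 0, the upper limit is 1.96 × √(2/70) = 0.331, so a reversal needs a shift above 0.50 − 0.331 = 0.169. Treating all 25% lost from the hub as 1 SD worse, and the ICAU losses as random, adds 0.25 and gives 0.581. That is an extreme case. At 10% the limit is 0.431 and the conclusion stands. ICAU clinicians also track progress by diary, ISI and Epworth scores, and nothing shows which arm would terminate more.
- **That the missing-data plan is useless.** Section {20c} allows for data missing not at random, {20a} already plans a likelihood-based repeated-measures model, and the choice of imputation and sensitivity analyses may sit in an analysis plan that is not shown.
- **That loss of eligibility also ends follow-up.** Section {11d} permits concomitant care "to the extent that eligibility criteria for the trial continue to be met". It limits care and says nothing about ending outcome collection.

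These objections limit the size and certainty of the harm. They leave the {11b} sentence as it is: it ends participation, no section provides for outcomes afterwards, and missing-data methods can bound the effect but not restore the values.

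**Conclusion.** The point holds as a conflict between {11b} and {20c}. Following the first loses outcomes for randomised participants whom the second says will be included. Removal rests on unblinded judgment without fixed criteria, by different clinicians in each arm, so it may be unequal.

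The amount of bias is unknown, and so is its direction. Shifts of 0.05 to 0.10 SD towards non-inferiority follow from assumed terminations of 10% or 15% in the hub against 5% in ICAU, a 1 SD gap, and a complete-case contrast. Other equally permissible inputs give no shift or one against the hub. The documents do not support saying that the trial's conclusion would change.

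A secondary point also holds: the choice of missing-data method should not wait on determining a mechanism that the observed data cannot reveal.

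**What to change.** **Main change.** Amend {11b} so that stopping treatment does not end outcome collection, and make {20c} agree. For every randomised participant, unless consent is withdrawn, continue the electronic ISI, PHQ-2 and GAD-2 at 6–8 weeks and at 3-month follow-up, and the two satisfaction surveys at 6–8 weeks only, as the Outcomes section {12} schedules them. When treatment stops remains the clinician's decision and is not judged here.

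**Secondary change.** In {20c}, name the method in advance instead of making it depend on the mechanism found. The mixed model already planned in {20a} could serve under missing at random. Add a sensitivity analysis that worsens the imputed values for missing hub outcomes by increasing amounts (delta) and reports the amount at which non-inferiority would be lost. If an analysis plan already contains this, a reference to it is enough.

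**Cost.** A short amendment, questionnaire access and reminders for a few more participants after treatment ends, and a small amount of extra analysis. The assessments are already electronic ({18a}, {19}).
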